## Abstract

**Background:**

Insufficient vitamin D status and increased renin-angiotensin system (RAS) activity have been associated with renal-vascular disease and nephropathy in diabetes. Accumulating evidence indicates that vitamin D receptor (VDR) activation lowers unfavorable RAS activity; however, more human intervention studies evaluating whether this mechanism could influence diabetic kidney disease are needed. We previously reported that both vitamin D levels and genetic variation at the VDR predict human RAS activity, and that vitamin D therapy can lower RAS activity in non-diabetics. The VALIDATE-D study is a randomized, placebo-controlled, intervention study designed to extend these findings by evaluating whether direct VDR activation in diabetes lowers circulating and local renal-vascular tissue RAS activity (Aims 1 and 2) in a manner similar to the action of ACE inhibitors (Aim 3).

**Methods/Design:**

Forty subjects with type 2 diabetes, microalbuminuria, and without chronic kidney disease will be recruited to undergo detailed assessment of the RAS before and after randomization to calcitriol 0.75 mcg/day or placebo. Primary analyses will evaluate whether calcitriol therapy reduces circulating and renal-vascular tissue-RAS activity in comparison to placebo. All subjects will thereafter be treated with lisinopril and followed for 3.5 months to evaluate whether combination therapy (calcitriol + lisinopril vs. placebo + lisinopril) additively or synergistically improves renal-vascular function, and lowers proteinuria.

**Discussion:**

The VALIDATE-D study is the first human intervention study to evaluate whether direct VDR activation can lower the human RAS in diabetes, compared to the effect of an ACE inhibitor, and whether this mechanism can translate to clinically relevant endpoints for diabetic kidney disease. The outcomes of VALIDATE-D will have major implications for the recommendation of vitamin D supplementation for the primary prevention of kidney complications in diabetes.

**Trial registration:**

ClinicalTrials.gov, NCT01635062

## Background

The link between vitamin D and kidney disease, particularly in the setting of human diabetes, has received much attention [1,2]. Observational and limited interventional studies have supported a renoprotective benefit to higher vitamin D levels and vitamin D supplementation [3-7]; however, there is a need for more dedicated human intervention studies to confirm these findings. One of the main proposed mechanisms linking vitamin D with renal-vascular and kidney disease is regulation of the renin-angiotensin system (RAS) [8,9]. Since both of these hormonal systems have complex genetic and environmental regulatory steps (Figure 1), carefully controlled interventional studies that evaluate both *mechanisms of action and clinical outcomes* are needed to distinguish the hormonal interplay that is likely involved for vitamin D therapy to influence kidney disease.

**Figure 1 F1:**
[figure not shown]
**The proposed interaction between vitamin D and RAS metabolism.** Renin catalyzes the conversion of angiotensinogen to angiotensin I, which is further converted to the vasoactive peptide angiotensin II. Angiotensin II is a direct vasoconstricter, and can also ilicit aldosterone secretion from the adrenal cortex. Under physiologic situations, activation of the RAS in response to renal-vascular hypo-perfusion serves to increase blood pressure and renal salt retention. However, in pathologic states (such as in diabetes and obesity), inappropriately high RAS activity contributes to vascular and kidney diseases. Vitamin D_3_ is largely produced in the skin with exposure to ultraviolet radiation, but may also be ingested orally. This precursor is hydroxylated to 25-hydroxyvitamin D (25[OH]D) and 25(OH)D serves as the stable barometer of clinical “vitamin D status.” Under the control of parathyroid hormone and calcium status, 25(OH)D can be hydroxylated to form the active vitamin D receptor (VDR) agonist 1,25-dihydroxyvitamin D (1,25[OH]_2_D). Activation of the VDR by 1,25(OH)_2_D is known to influence the regulation and expression of a myriad of genes, including renin.

Both excess activity of the renin-angiotensin system (RAS) and insufficient vitamin D status have been implicated in the development of renal-vascular disease that results in diabetic nephropathy [1,2,10]. The RAS can mediate renal-vascular disease via its circulating components, and additionally the locally expressed renal-vascular tissue-RAS also contributes to the development of kidney disease [11,12]. Excess renal-vascular tissue-RAS activity has been implicated in the development of diabetic nephropathy; RAS inhibitors [13-15], as well as favorable vitamin D status [5,16,17], may mitigate this effect.

Animal studies have shown that the activation of the vitamin D receptor (VDR) by 1,25-dihydroxyvitamin D (1,25[OH]_2_D) negatively regulates renin expression and thereby lowers RAS activity [9,18] (Figure 1). In mouse models of diabetes, both VDR-agonists and RAS-inhibitors blunted the development of diabetic nephropathy when given alone, but the combination (VDR-agonist + RAS-inhibitor) *synergistically* prevented the development of diabetic nephropathy via down-regulation of the renal-vascular tissue-RAS [19-21]. We, and others, have reported findings that translate these animal experiments to humans: the combination of vitamin D levels and genetic variation at the human VDR predicts RAS activity [22-24]. Large observational studies have shown that the prevalence of chronic kidney disease and proteinuria (a marker of kidney disease progression) are associated with lower 25(OH)D levels [3,25,26]. Due to their cross-sectional design, these aforementioned studies could not reveal causality or confirm the mechanism linking vitamin D-VDR interactions and renal outcomes. A few human interventions have demonstrated that VDR agonists may reduce proteinuria [2,7], but these studies were confined to populations with established chronic kidney disease (CKD), and evaluation of the RAS was not undertaken. We recently completed a pilot human intervention study in non-diabetics without CKD that demonstrated that high-dose vitamin D_3_ therapy improved renal-vascular hemodynamics by lowering renal-vascular tissue-RAS activity [5]. This latter effect was similar to that induced by an angiotensin converting enzyme (ACE) inhibitor, thereby further supporting a renoprotective effect of vitamin D therapy [5].

In light of these novel human results translated from animal experiments, we hypothesize that activation of the VDR represents a method to lower renal-vascular tissue-RAS activity in human diabetes, and could therefore play an important role in the *primary prevention* of diabetic nephropathy. We therefore designed the VALIDATE-D study: an ongoing randomized, double-blinded, placebo-controlled study to assess whether direct VDR activation: Aim 1) lowers circulating RAS activity in human diabetes; Aim 2) lowers renal-vascular tissue-RAS activity in human diabetes; and Aim 3) in combination with ACE inhibition, exerts an additive or synergistic effect on the renal-vascular tissue-RAS and proteinuria.

## Methods/Design

### Study population and recruitment

The VALIDATE-D study will enroll 40 adults, aged 18–70 years, with Type 2 diabetes (T2DM), microalbuminuria, and without known CKD (estimated glomerular filtration rate > 60 mL/min). Subjects will be recruited from the local community and from the outpatient clinics of the Division of Endocrinology, Diabetes, and Hypertension within the Department of Medicine at Brigham and Women’s Hospital, Boston, USA. Eligibility will be assessed at an in-person screening visit involving detailed history, physical examination, and laboratory assessment.

Inclusion criteria include T2DM that is controlled with diet, oral hypoglycemic agents, incretin analogues, or a single basal insulin injection; microalbuminuria; normal blood pressure or stage 1 hypertension treated with 0–1 antihypertensive agents; and normal blood cell counts, liver function, and electrocardiogram.

Exclusion criteria include CKD (glomerular filtration rate < 60 mL/min); poorly controlled T2DM (defined as HbA1c > 8.5% or the use of >1 daily insulin injection or a history or retinopathy); stage 2–3 hypertension or the use of more than one antihypertensive agent; kidney stones, parathyroid or granulomatous disorders, liver or heart failure, or coronary artery disease or congestive heart failure or cerebrovascular accidents. All subjects provide informed consent, and all study procedures have been approved by the Brigham & Women’s Hospital institutional and ethics board as well as the Brigham and Women’s Hospital Center for Clinical Investigation. Recruitment was initiated in September 2012 and is expected to be completed by September 2016.

### Study protocol overview

A detailed study schema is shown in Figure 2. All study visits will occur in the Clinical Research Center (CRC) at Brigham and Women’s Hospital. Studies will be performed in the CRC in order to control posture, time of day, dietary intake, and medication administration, since all of these factors are known to influence RAS activity. In brief, detailed profiling of the RAS will be performed at baseline before any intervention (Visits 2 & 3), again after double-blinded randomization to calcitriol or placebo (Visits 5 & 6) to assess whether calcitriol lowers RAS activity, and again after the addition of lisinopril to the blinded study drug to assess for an additive or synergistic relationship between VDR-agonist and ACE inhibitor therapy on the RAS and proteinuria (Visits 8 & 13).

**Figure 2 F2:**
[figure not shown]
***VALIDATE-D study schema*****: subjects will be screened and then may undergo a medication washout to withdraw interfering anti-hypertensive medications (when applicable).** Aim 1: The *circulating* RAS will be assessed on LS diet before and after randomization to calcitriol/placebo (visits 2 & 5). Aim 2: The *renal-vascular tissue-RAS* will be assessed on HS diet before and after calcitriol/placebo (visits 3 & 6). Aim 3: All subjects will then receive lisinopril 5 mg/d in addition to calcitriol/placebo to assess the impact of combination therapy (calcitriol + lisinopril vs. placebo + lisinopril) on the renal-vascular tissue-RAS (visits 6 & 8) and proteinuria (visits 6, 8, 13). Serum calcium and phosphate will be monitored weekly throughout the study for safety, at each visit and at designated safety checks (visits 4, 7, 9–12).

#### Washout

It is well known that many medications interfere with physiologic RAS responses or with the assays that measure the RAS. To optimize the reliability and accuracy of RAS measurements, medications that interfere with RAS assessments will be withdrawn. Subjects using RAS inhibitors (such as angiotensin converting enzyme [ACE] inhibitors, angiotensin receptor blockers, or mineralocorticoid receptor antagonists) will stop their medications for 2 months prior to study. Subjects using beta-blockers or diuretics will stop their medications for 1 month prior to study, whereas those on calcium channel blockers will stop for 2 weeks prior to study. Medication washout will be supervised by a study staff based on previously described safety protocols [5] after providing and instructing each subject on how to use a home sphygmomanometer. As previously described, in cases where hypertension (159/99 mmHg) results following withdrawal of an antihypertensive medication, amlodipine will be used to lower blood pressure as it has a neutral effects on RAS activity.

#### Study diets

All study procedures will be conducted using one of two specifically designed study diets.

### Low-salt diet

The low salt (LS) diet includes 10 mEq of sodium, 100 mEq of potassium, and <600 mg of calcium per day. The purpose of this diet is to induce *maximal stimulation* of RAS components to allow for adequate measurements of the *circulating RAS*. Subjects will consume the LS diet for 1 week prior to study visits where the circulating RAS will be measured (Visits 2 and 5). All daily meals and food intake during the LS dietary phase will be prepared and provided to study participants by the CRC dietary kitchen staff.

### High-salt diet

The high sat (HS) diet includes 200 mEq of sodium, 50 mEq of potassium, and <600 mg of calcium per day. The purpose of this diet is to induce *maximal suppression* of the circulating RAS components in order to most effectively measure the *renal-vascular tissue-RAS*, as previously described [5,17]. Subjects will consume the HS diet for 1 week prior to study visits where the renal-vascular tissue-RAS will be evaluated (Visits 3, 6, and 8). The HS diet involves consumption of an ad lib diet, with supplements provided to achieve the sodium and potassium contents.

### Low calcium diet

Subjects will be instructed and taught to restrict dietary calcium intake during the LS and HS dietary phases (<600 mg/day), and also during the duration of the study in between study visits (<1000 mg/day). The purpose of calcium restriction is to minimize the risk of hypercalcemia and hyperphosphatemia associated with calcitriol administration; this risk is negligible in the context of low dietary calcium intake [27-29]. A registered dietician will coach subjects throughout the study on restricting calcium intake and will provide materials to guide dietary intake at home (Dietary Calcium Intake Recommendations Additional file 1). Compliance with study diets will be confirmed by 24-hour urine collections obtained at every study visit.

#### Baseline assessments of the circulating and renal-vascular tissue-RAS (Visits 2 & 3)

After a screening visit (Visit 1) and a potential antihypertensive washout phase, all subjects will undergo baseline assessments to characterize the circulating and renal-vascular tissue-RAS.

### Circulating RAS on LS diet (Visit 2)

Study visit 2 is designed to measure the baseline circulating RAS under conditions designed to induce maximal stimulation of the circulating RAS: restricted dietary sodium intake and upright posture. After one week of LS diet consumption, subjects are studied at 8 AM in the morning (Figure 2). Subjects will maintain an upright standing posture for at least 1 hour. Blood samples are obtained at the end of the postural phase to measure circulating RAS components (plasma renin activity, angiotensn II, aldosterone).

### Renal-vascular tissue-RAS on HS diet (Visit 3)

Study visit 3 is designed to assess baseline renal-vascular tissue-RAS activity by measuring changes in renal plasma flow (RPF) in response to an infusion of exogenous angiotensin II. Angiotensin II is a vasopressor that specifically interacts with angiotensin receptors to induce renal-vascular vasoconstriction resulting in a decrease in RPF. *The magnitude of the decline in RPF to angiotensin II is inversely related to renal-vascular tissue-RAS activity* (Figure 3); greater renal-vascular responses to angiotensin II signify lower local tissue-RAS activity [5,30,31]. Using this physiologic methodology, measurement of RPF responses to angiotensin II provide an indirect method to assess the human renal-vascular tissue-RAS.

**Figure 3 F3:**
[figure not shown]
**Reciprocal relationship between renal-vascular tissue-RAS activity and the renal-vascular response to angiotensin II.** A blunted response to angiotensin II reflects a high level of local, endogenous, renal-vascular tissue-RAS activity (the smaller the decline in renal plasma flow in response to an infusion of angiotensin II, the greater the activity of the local renal-vascular tissue-RAS). Conversely, a robust response to angiotensin II is observed when tissue-RAS activity is low.

To adequately measure the renal-vascular tissue-RAS, subjects are studied on a HS diet and in overnight supine posture to suppress endogenous circulating RAS components, thereby amplifying measurable RPF responses to angiotensin II [32]. After completing one week of HS diet, subjects will be admitted to the CRC and maintained supine overnight and throughout the study procedures on the following morning. In the morning, two intravenous lines will be placed to facilitate infusion of study drugs and frequent blood sampling. Weight-based *para-*aminohippurate (PAH) will then be infused and its clearance used to measure RPF throughout the duration of the study visit [5]. After allowing PAH concentrations to reach a steady state over 60 minutes, blood will be sampled to establish the baseline RPF. Angiotensin II will then be infused at 0.3 ng/kg/min for 45 minutes and escalated to 1 ng/kg/min for an additional 45 minutes to assess dose–response characteristics. PAH will be measured during and after each angiotensin II infusion to measure RPF dynamics. Blood pressure will be monitored closely throughout the infusions based on standardized safety protocols [5] that we have extensive experience performing in our CRC. The study visit will end upon completion of the angiotensin II infusions, and subjects will be discharged to undergo randomization to the study drug.

#### Randomization to study drug

Following study visit 3, subjects will be randomized to either calcitriol 0.75 mcg/day or placebo arm using a 2 block randomization. Double-blinded randomization will be performed by the investigational drug pharmacy at our institution, and neither the subjects nor the investigators will know the identity of the randomized study drug.

#### The influence of calcitriol on the RAS (Visits 5 & 6)

### Circulating RAS on LS diet (Visit 5)

After 2 weeks of daily calcitriol or placebo, subjects will return on LS diet and complete visit 5, which is identical to visit 2. Aim 1 of this study (to assess whether direct VDR activation lowers circulating RAS activity in human diabetes) is executed in study visits 2 and 5. *Anticipated Results:* It is anticipated that calcitriol therapy will lower circulating RAS components (plasma renin activity and angiotensin II) when compared to placebo, demonstrating for the first time that VDR agonism can inhibit the circulating RAS in human diabetes.

### Renal-vascular tissue-RAS on HS diet (Visit 6)

After a third week on the study drug, subjects will return on HS diet for an overnight CRC study visit 6, that is identical to Visit 3. This visit will permit assessment of study Aim 2 (to assess whether direct VDR activation lowers renal-vascular tissue-RAS activity in human diabetes) by comparing the renal-vascular tissue-RAS activity before and after calcitriol/placebo. *Anticipated Results:* It is anticipated that calcitriol therapy will raise basal RPF and increase the RPF sensitivity to angiotensin II, thereby demonstrating that VDR activation improves renal-vascular hemodynamics by lowering local renal-vascular RAS activity in human diabetics without CKD.

#### The influence of combination VDR-agonist and ACE inhibitor therapy on the renal-vascular tissue RAS (Visit 8)

Upon completing study visit 6, all subjects will receive lisinopril (initially 2.5 mg daily, which will be increased to 5 mg daily after one week, unless blood pressures are below 90/50 mmHg or subjects experience orthostatic symptoms) in addition to their randomized study drug (Figure 2). After 2 weeks of daily combined therapy (calictirol + lisinopril or placebo + lisinopril), subjects will return on the HS diet for a final inpatient CRC visit that is identical to study visits 3 & 6. Comparing the outcomes of study visits 6 and 8 will permit evaluation of Aim 3 of this study (to assess whether direct VDR activation in combination with ACE inhibition exerts an additive or synergistic effect on the renal-vascular tissue-RAS and proteinuria). *Anticipated Results:* Combination therapy (calcitriol + lisinopril) will additively or synergistically raise RPF and increase the RPF sensitivity to angioensin II infusion, reflecting decreased renal-vascular tissue-RAS activity when compared to placebo + lisinopril.

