#### The influence of chronic combination therapy on proteinuria (Visit 13)

Following completion of study visit 8, subjects will be discharged home to continue both the study drug and lisinopril for three months of long-term therapy (Figure 2). For the final visit of the study, subjects will return after one week of HS diet with a completed 24-hour urine collection, which will be analyzed for protein. The 24-hour urine protein measured at this visit will be compared using repeated measures analyses to the urine protein levels obtained from 24-hour urine collections completed at each inpatient visit on HS dietary balance (visits 3, 6, 8). *Anticipated Results:* Combination therapy (calcitriol + lisinopril) will additively or synergistically lower proteinuria when compared to placebo + lisinopril, thereby paralleling prior animal studies that showed that the combination of VDR agonist + conventional RAS inhibitor therapy induced synergistic renoprotective benefits in mouse models of diabetes [19-21].

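### For the renal-vascular tissue-RAS, the Visit 6 to Visit 8 change compared between arms tests only synergy; the additive half of Aim 3 needs a between-arm contrast at Visit 8

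*Protocol article*

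**What the plan says.** All references are to the protocol article.

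- **Aim.** The Visit 8 section gives Aim 3 as whether VDR activation combined with ACE inhibition "exerts an additive or synergistic effect on the renal-vascular tissue-RAS and proteinuria".
- **Named comparison.** The same section says "Comparing the outcomes of study visits 6 and 8 will permit evaluation of Aim 3 of this study". The Figure 2 caption assigns the same visits: "on the renal-vascular tissue-RAS (visits 6 & 8) and proteinuria (visits 6, 8, 13".
- **Timeline.** "Following study visit 3, subjects will be randomized to either calcitriol 0.75 mcg/day or placebo arm"; "After a third week on the study drug, subjects will return on HS diet for an overnight CRC study visit 6"; "Upon completing study visit 6, all subjects will receive lisinopril". Visit 8 follows two weeks of combined therapy, and Visit 13 follows a further three months.
- **Type of analysis.** The Outcomes section plans paired and repeated-measures analyses within individuals, and non-paired comparisons of changes between the calcitriol and placebo groups.
- **A second description of Aim 3.** The Abstract, the Figure 2 caption, the anticipated results for Visits 8 and 13, and the Discussion all set the combination arm against the arm on lisinopril with placebo.
- **Proteinuria visits.** The Figure 2 caption has "and proteinuria (visits 6, 8, 13". The Visit 13 section compares Visit 13 with the collections "completed at each inpatient visit on HS dietary balance (visits 3, 6, 8", which brings in the pre-randomisation visit.

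**The concern.** Each aim in Figure 2 is given a pair or set of visits, and for Aims 1 and 2 the pair is before and after study drug. Read the same way, and together with the Outcomes section, the tissue-RAS part of Aim 3 becomes a between-arm comparison of the change from Visit 6 to Visit 8. By Visit 6 the calcitriol arm has had three weeks of drug, so subtracting the Visit 6 value removes whatever calcitriol has already done. What is left is the effect of adding lisinopril, which both arms receive.

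If that contrast governs, a true additive benefit gives an expected difference of zero and could be reported as no benefit of the combination. The paired change within the calcitriol arm could be misread in the other direction, because it will look favourable whenever lisinopril works. The aim has two halves, additive and synergistic, and the named pair of visits serves only the second.

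**Working it through.** **The plan's own figure.** There is none for this point: the article gives no effect size, SD or power for Aims 2 and 3, only a pilot of 14 subjects. Its one reproducible sample size is 5 per arm for Aim 1 (difference 1, SD 0.54, power 0.9, paired). The normal approximation is (0.54 × (1.960 + 1.282) / 1)² = 3.06; adding 1.960²/2 = 1.92 for small samples gives 4.98, so 5. It has no bearing on Aim 3.

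**Step 1: expected values.** Let *C* be the calcitriol effect, *L* the lisinopril effect, *I* the interaction, and *T6*, *T8* the period effects common to both arms, all relative to Visit 3.

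| Visit | Placebo arm | Calcitriol arm | Difference between arms |
|---|---|---|---|
| 3 | 0 | 0 | 0 |
| 6 | T6 | T6 + C | C |
| 8 | T8 + L | T8 + C + L + I | C + I |

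- Between-arm difference in the Visit 6 to 8 change: (L + I + T8 − T6) − (L + T8 − T6) = **I**.
- Between-arm difference at Visit 8, or in the change from Visit 3: **C + I**.
- Paired Visit 6 to 8 change within the calcitriol arm: L + I + T8 − T6. It does not contain C.

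Under additivity (I = 0) the first contrast is zero for every value of C. This result needs no assumption about SD or correlation.

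**Step 2: size, under assumed inputs.** From the article: 20 per arm, two-sided 0.05. Assumed, because the article does not give them: SD 1 at each visit, C = L = 0.6 SD, and a common between-visit correlation of 0.5, 0.7 or 0.9. There were 20,000 simulated trials per setting. Entries are rejection rates in % at correlation 0.5 / 0.7 / 0.9.

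| Truth | Visit 6–8 change, between arms | Visit 8 adjusted for Visit 3, between arms | Paired Visit 6–8, calcitriol arm |
|---|---|---|---|
| No calcitriol effect (C = 0, I = 0) | 5.2 / 5.0 / 5.3 | 4.9 / 4.9 / 5.0 | 72.0 / 90.9 / 100 |
| Additive (C = 0.6, I = 0) | 5.2 / 5.0 / 5.2 | 55.3 / 72.5 / 98.7 | 71.8 / 91.0 / 100 |
| Synergy (C = 0.6, I = 0.3) | 15.8 / 22.0 / 55.1 | 88.5 / 96.9 / 100 | 96.8 / 99.9 / 100 |
| Full overlap (C = 0.6, I = −0.6) | 45.8 / 65.9 / 98.5 | 4.9 / 5.0 / 4.9 | 5.0 / 5.0 / 4.9 |

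The first two rows cannot be told apart in the first or third result column. Only the between-arm contrast at Visit 8 separates them. In the additive row the unadjusted change from Visit 3 also responds (45.2 / 67.1 / 98.5). In the last row the first two contrasts reverse roles, so they answer different questions.

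A hand check of the additive row for Visit 8 adjusted for Visit 3: the standard error is √(1 − ρ²) × √(2/20), that is 0.866 × 0.316 = 0.274 at ρ = 0.5 and 0.436 × 0.316 = 0.138 at ρ = 0.9. The ratios 0.6/0.274 = 2.19 and 0.6/0.138 = 4.35 agree with power near 55% and 99%.

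**Step 3: time on calcitriol.** Exposure is 3 weeks at Visit 6, 3 + 2 = 5 weeks at Visit 8, and about 5 + 13 = 18 weeks at Visit 13. No arm continues calcitriol without lisinopril after Visit 6. If the calcitriol effect grows by *G* between Visits 6 and 8, the between-arm change contrast estimates I + G. Growth of 0.3 SD with no interaction would therefore give the same rates as the synergy row, 15.8 / 22.0 / 55.1. The article gives no information on G.

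**The case against.** A reader might infer that all of Aim 3 is to be judged on the Visit 6 to 8 change, and that the trial therefore cannot detect an additive benefit. The article does not support that.

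- The Visit 8 section speaks of comparing outcomes, not changes; taking it as change from Visit 6 is an inference from Figure 2 and the Outcomes section. Comparing the arms at each of the two visits would give C and then C + I, which separates the two halves of the aim.
- The article repeatedly describes a comparison of the two lisinopril-treated arms, and that contrast does respond to an additive benefit.
- Visit 6 being post-randomisation does not invalidate the contrast. A between-arm difference in the Visit 6 to 8 change is still a randomised comparison, and Visit 6 is the right reference for interaction.
- For proteinuria the Visit 13 section includes Visit 3, and the Figure 2 caption lists visits without calling Visit 6 a baseline. Blindness to additivity cannot be asserted there; the two visit lists simply differ.
- The size of the power loss rests on assumed inputs, and an article may leave covariate adjustment and the ranking of contrasts to an analysis plan.

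All of this limits the point. What remains is that the Methods attach one pair of visits to an aim with two halves, that the natural contrast from that pair serves one half only, and that the contrast serving the other half is described elsewhere without being tied to it. On the same data the two can give opposite answers, and nothing says which governs.

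**Conclusion.** The point holds for the renal-vascular tissue-RAS. The between-arm difference in the Visit 6 to 8 change is a test of interaction. It is zero under additivity whatever calcitriol does, and the paired change in the calcitriol arm then shows only lisinopril plus any period effect. Neither can support an additive claim. The comparison of the two lisinopril-treated arms can, so the article contains the right contrast but does not assign it to that claim.

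The zero expectation is algebra. It assumes that additivity is judged on the scale analysed and that the calcitriol effect is steady from Visit 6 to Visit 8. The rates (about 5% against about 55% to 99%) hold for an assumed 0.6 SD effect and correlation 0.5 to 0.9, and would move with other values. Even for synergy the change contrast is weak: about 16% to 55% for an assumed interaction of 0.3 SD. For proteinuria only the disagreement over Visit 3 is established.

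**What to change.** 1. **Added benefit.** State that it is tested by the between-arm contrast, calcitriol with lisinopril against placebo with lisinopril, at Visit 8 for renal plasma flow and its response to angiotensin II, and at Visit 13 for urine protein, each adjusted for the pre-randomisation Visit 3 value.
2. **Synergy.** Keep the between-arm difference in the Visit 6 to 8 change, labelled as the test of departure from additivity only. State that it is read on the assumption that the calcitriol effect has plateaued by Visit 6, since no arm continues calcitriol without lisinopril. Wording cannot remove that design limit.
3. **Consistency.** List proteinuria Visits 3, 6, 8 and 13 in both Figure 2 and the Visit 13 section, and bring the Visit 8 section, Outcomes and Discussion into line with items 1 and 2.

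The cost is wording in the protocol or analysis plan, settled before unblinded analysis. All the visits and measurements are already scheduled.
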